## Outcome Measures

### Primary Outcome Measure:

1. Change in happiness from baseline using the subjective happiness scale  
The Subjective Happiness Scale consists of four items: (1) “In general, I consider myself \_\_\_\_\_.” Responses options run from 1 = “not a very happy person” to 7= “a very happy person.” (2) “Compared to most of my peers, I consider myself \_\_\_\_\_” with response options from 1 = “less happy” to 7 = “more happy.” (3) “Some people are generally very happy. They enjoy life regardless of what is going on, getting the most out of everything. To what extent does this characterization describe you?” (1 = “not at all” to 7 = “a great deal”). (4) “Some people are generally not very happy. Although they are not depressed, they never seem as happy as they might be. To what extent does this characterization describe you?” (1= “not at all” to 7= “a great deal”; reverse coded) These four items will be averaged into a scale ranging from 1-7, where higher scores indicate greater subjective happiness.

[Time Frame: baseline, end of weeks 1, 2, 3, and 5]

2. Change in valued life assessment from baseline using 4-item scale  
Respondents' individual perceptions of whether their life has value will be measured using the valued life subscale developed by Morgan and Farsides. This measure will consist of the average of the following four items: (1) “My life is worthwhile,” (2) “My life is significant,” (3) I really value my life,” and (4) I hold my own life in high regard.” In each instance, response options will run from -3 = “strongly disagree” to 3 = “strongly agree”.

[Time Frame: baseline, end of weeks 1, 2, 3, and 5]

3. Change in depression from baseline using the CESD (8-item)  
Depression will be measured using the well-established 8-item short-form of the Centre for Epidemiological Studies-Depression Scale (CES-D). Respondents will report how often in the past week they (1) felt depressed, (2) felt that everything was an effort, (3) felt that sleep was restless, (4) felt happy (reverse coded), (5) enjoyed life (reverse coded), (6) felt lonely, (7) felt sad, and (8) could not get going. Responses will be scored where 0 = “rarely or none of the time,” 1 = “some of the time,” 2 = “a moderate amount of time,” and 3 = “most or all of the time.”

[Time Frame: baseline, end of weeks 1, 2, 3, and 5]

4. Change in anxiety from baseline using the HADS-A  
Anxiety will be measured with the Hospital Anxiety and Depression Scale—Anxiety (HADS-A), which is both commonly used and well-validated. This is a 7-item scales that asks respondents how often in the past week they: (1) felt tense or wound up, (2) got a frightened feeling as if something awful was about to happen, (3) had worrying thoughts go through their mind, (4) got a frightened feeling like butterflies in the stomach, (5) felt restless as if they had to be on the move, (6) had a sudden feeling of panic, and (7) could sit at ease and feel relaxed. To ensure consistency with our measure of depression, responses will be coded where 0 = “rarely or none of the time,” 1 = “some of the time,” 2 = “a moderate amount of time,” and 3 = “most or all of the time.”

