Respondents will be contacted for the first three days each week and asked to report what they did. At the end of weeks 1, 2, and 3 they will complete a longer survey that repeats the same measures of emotional well-being and mental health used at baseline. At this point the intervention will be complete. The investigators will recontact respondent two weeks later (at the end of week 5) to assess whether the intervention has a lasting effect on mental health and emotional well-being. This final survey will also include a measure of whether or not respondents continued their assigned behaviors following the end of the intervention. This measure might be useful for explaining any lasting effects in exploratory analyses.

The expected effect size is  $d = 0.19$ . The research team will assess experimental effects using multiple linear regression. The models will include indicator variables for experimental conditions as well as controls for baseline levels of happiness, valued life, depression, and anxiety. These baseline measures should be unrelated to experimental conditions (which will be randomly assigned) so including them will increase the efficiency of estimates. Under the assumption that these variables will account for at least 50% of the variance in the outcomes, the sample size needed to detect an effect of size  $d = 0.19$  with 95% power is  $N = 357$  or approximately 360 per condition. The

expected attrition rate is 30% after baseline which means that the investigators will sample  $360/0.7 = 514$  per condition.

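### The anxiety outcome gives no reverse coding for its one positively worded item; scored literally, one of seven items in a primary outcome and in a baseline covariate is mis-keyed

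*Protocol*

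**What the plan says.** All the scoring text is in the Protocol, Outcome Measures, under the four primary outcomes.

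- **Anxiety (outcome 4, HADS-A).** The scale is introduced with "This is a 7-item scales that asks respondents how often in the past week they". Six symptom items follow, among them "5) felt restless as if they had to be on the move, (6) had a sudden feeling of panic". The list closes with the positively worded item: "6) had a sudden feeling of panic, and (7) could sit at ease and feel relaxed". The coding rule comes directly after it: "could sit at ease and feel relaxed. To ensure consistency with our measure of depression, responses will be coded where 0". The rule runs to 3 for most or all of the time. There is no reversal note, no statement of whether items are summed or averaged, and no statement of what a high score means.
- **Depression (outcome 3, CES-D).** The same 0-3 coding is used, and the positively worded items are marked: "4) felt happy (reverse coded), (5) enjoyed life (reverse coded".
- **Happiness (outcome 1).** The fourth item is marked, and the scale is then defined: "reverse coded) These four items will be averaged into a scale ranging from 1-7". The direction of the score is stated.

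The Detailed Description adds that baseline anxiety is one of four baseline covariates in the regression models. Nothing elsewhere in the protocol supplies a reversal for item 7.

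**The concern.** Item 7 points the opposite way from items 1 to 6. Under the stated coding, a respondent who is relaxed most of the time gets 3 on item 7, the same value that a respondent who panics most of the time gets on item 6.

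The protocol has four opposite-keyed items across these scales: one in happiness, two in the CES-D and one in the HADS-A. Only the last is unmarked. A reader who follows the document's own convention would leave item 7 as it stands. The usual key of the instrument cannot simply be assumed to fill the gap, because the protocol sets its own response coding for this scale.

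At stake are the reliability and scale of one of four primary outcomes and the usefulness of a baseline covariate. Anyone rescoring the shared data from this text could also fail to reproduce the investigators' scores.

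**Working it through.** **1. The plan's own sample size.** Inputs from the Detailed Description: d = 0.19, power 95%, R² = 0.50 from the baseline covariates, 357 (about 360) per condition. The significance level is not stated there; two-sided 0.05 is assumed.

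n = 2(1 − R²)(1.960 + 1.645)² / d² = 2 × 0.50 × 12.996 / 0.0361 ≈ 360 per condition.

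This agrees with the stated figure to within 1%. Power is 95.0% at 360 and 94.8% at 357.

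**2. Score range (sum of seven items).** Correctly keyed: least anxious 0, most anxious 7 × 3 = 21. Item 7 unreversed: least anxious 6 × 0 + 3 = 3, most anxious 6 × 3 + 0 = 18. The distance between the two extremes falls from 21 to 15.

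**3. Model for reliability and effect.** Assume seven items of equal variance with a common inter-item correlation r once correctly keyed. The documents give no value for r, so 0.3 to 0.6 is shown.

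- Variance of the correct sum: 7 + 42r.
- Variance with item 7 unreversed: 7 + 30r − 12r = 7 + 18r.
- Alpha = (7/6)(1 − 7/variance of the sum).
- If all items shift equally, the raw effect ratio is (6 − 1)/7 = 5/7 = 0.71, a 29% loss. It is the same for a sum or a mean.
- The standardised effect ratio is (5/7) × √[(7 + 42r)/(7 + 18r)].
- Power = Φ(d / √[2(1 − R²)/n] − 1.960), with R² held at 0.50.

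| r | alpha, correct | alpha, unreversed | effect ratio | d | power at 360 | n per condition for 95% |
|---|---|---|---|---|---|---|
| 0.3 | 0.750 | 0.508 | 0.898 | 0.171 | 89.9% | 447 |
| 0.4 | 0.824 | 0.592 | 0.925 | 0.176 | 91.5% | 421 |
| 0.5 | 0.875 | 0.656 | 0.945 | 0.180 | 92.6% | 404 |
| 0.6 | 0.913 | 0.708 | 0.961 | 0.183 | 93.4% | 391 |

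**4. If item 7 responds less than the others.** Let item 7 shift by s times the shift of the other items. The standardised ratio is then [(6 − s)/(6 + s)] × k, with k = √[(7 + 42r)/(7 + 18r)]. It equals 1 when s = 6(k − 1)/(k + 1).

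- r = 0.3: k = 1.257, break-even s = 0.68.
- r = 0.6: k = 1.345, break-even s = 0.88.

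Above these values the standardised effect shrinks; below them it grows, because the mis-keyed item also lowers the score's variance. At s = 0.5 it rises by 6-14%. At s = 0 the raw difference is unchanged and the standardised effect rises by 26-35%.

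**The case against.** The strongest reply is that a missing label is not a scoring plan. The protocol never says that item 7 is left unreversed. Its CES-D paragraph has the same structure, a general 0-3 sentence after an item list that contains reversed items, so that sentence alone does not exclude reversal. The instrument is a named, established one, and the aim stated in "To ensure consistency with our measure of depression, responses will be coded where 0" refers to a measure whose positive items are reversed. The SAP and analytic code are listed as separate documents and may contain the reversal. An omission in drafting is plausible.

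Much of this stands, and it limits what can be claimed. A reader might infer that the trial's anxiety outcome was mis-scored; the documents cannot show that. A reader might also infer that mis-keying shrinks any effect, or that 29% of the effect is lost. The first holds only if item 7 moves nearly as much as the others, and the 29% is on the raw score only. Nor does a null anxiety result become a likely artefact when power stays near 90%.

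What does not stand is that the matter belongs wholly to the SAP. The protocol chose to fix item-level reversal in this section and did so for every other opposite-keyed item. The stated aim of consistency with the depression measure makes the gap an internal inconsistency.

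**Conclusion.** The point holds as a defect in the definition of a primary outcome. Applied literally, the stated coding mis-keys one of seven anxiety items, both in the outcome and in the baseline covariate.

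The change in score range is arithmetic and needs no assumption beyond summing. The fall in alpha rests on equal variances and the assumed correlations. The loss of up to about 10% in standardised effect, and of two to five percentage points of power, also needs item 7 to respond as much as the other six and R² to stay at 0.50. Lower reliability could reduce R² further; that is not quantified here. Under randomisation, a noisier baseline covariate costs precision and does not bias the comparison.

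The conclusion concerns what the text prescribes, not what the analysis did.

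**What to change.** In primary outcome 4, add '(reverse coded)' after item 7, as is done for the CES-D items. State whether the seven items are summed or averaged, and that higher scores mean greater anxiety. Confirm that the scoring code applies the reversal at baseline and at the end of weeks 1, 2, 3 and 5.

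The cost is one phrase and one sentence in the outcome definition and a check of one line of code. The protocol lists the study as completed, but no new data are needed: if the code turns out not to reverse the item, the anxiety score can be recomputed from the item responses and the models rerun. There is no statistical downside.

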## Eligibility

Minimum Age: 18 Years

Maximum Age:

Sex: All

Gender Based: No

Accepts Healthy Volunteers: Yes

Criteria: Inclusion Criteria:

- Canadian and American respondents from the Amazon Mechanical Turk

Exclusion Criteria:

Respondents will be excluded from the study if any of the following apply:

1. A respondent completes the baseline study unrealistically quickly. We measure response speed using the average number seconds spent on each survey item (seconds per item, or SPI). We judge a response to be unrealistically fast if its SPI value is less than 1. SPI calculations will exclude optional items.
2. A respondent does not complete at least half of the items in the baseline survey.
3. A respondent provides off-topic, non-sensical (e.g., random or gibberish words), or non-English responses to an open-ended question in the baseline survey. The open-ended question follows a dictator game (that is not part of the pre-registered portion of the study) and asks respondents what they hoped to accomplish by acting as they did during the dictator game. The specific nature of this question will make it straightforward to detect off-topic responses. A comment must be judged as off-topic, non-sensical, or non-English by two members of the research team to be excluded.
4. A respondent does not agree to continue with the study when asked if they wish to continue taking part in the study at the end of the baseline study, or in private correspondence with the researchers.
5. A respondent completes the baseline study using an IP address from outside Canada or the United States, or that appears to originate from a VPS or other suspicious source.
6. Technical difficulties prevent a respondent from completing the baseline study.

Because obtain sufficient power to detect effects is a central aim of this study, the investigators will replace respondents who are removed for reasons 1-5 in a rolling fashion. In the case of technical failure (#6), the first approach will be to resolve the issue and administer the baseline survey to the same participant. If this is not possible, a replacement will be recruited.

## IPDSharing

Plan to Share IPD: Yes

Using an OSF repository, other researchers and readers of the published study will have access to the IPD.

Supporting Information:

Study Protocol  
Statistical Analysis Plan (SAP)  
Informed Consent Form (ICF)  
Analytic Code

Time Frame:

After the publication of the paper and perpetually. The investigators plan to publish the study as a registered report, so study information will also be available as part of the report protocol.

Access Criteria:

URL: <https://osf.io/63yg9/>

